# A video-based transdiagnostic REBT universal prevention program for internalizing problems in adolescents: study protocol of a cluster randomized controlled trial

**DOI:** 10.1186/s12888-018-1684-0

**Published:** 2018-04-13

**Keywords:** Transdiagnostic, Video-based, Rational emotive behavioral therapy, Internalizing problems, Anxiety, Depression, Universal prevention, Adolescent, School intervention, Mechanisms of change

## Abstract

**Background:**

Internalizing problems are the most prevalent mental health problems in adolescents. Transdiagnostic programs are promising manners to treat multiple problems within the same protocol, however, there is limited research regarding the efficacy of such programs delivered as universal prevention programs in school settings. Therefore, the present study aims to investigate the efficacy of a video-based transdiagnostic rational emotive behavioral therapy (REBT) universal prevention program, for internalizing problems. The second objective of the present paper will be to investigate the subsequent mechanisms of change, namely maladaptive cognitions.

**Methods:**

A two-arm parallel randomized controlled trial will be conducted, with two groups: a video-based transdiagnostic REBT universal prevention program and a wait list control. Power analysis indicated that the study will involve 338 participants. Adolescents with ages between 12 and 17 years old, from several middle schools and high schools, will be invited to participate. Assessments will be conducted at four time points: baseline (T_1_), post-intervention (T_2_), 3 months follow-up (T_3_) and 12 months follow-up (T_4_). Intent-to-treat analysis will be used in order to investigate significant differences between the two groups in both primary and secondary outcomes.

**Discussion:**

This is the first randomized controlled trial that aims to investigate the efficacy and mechanisms of change of a video-based transdiagnostic REBT universal prevention program, delivered in a school context. The present study has important implications for developing efficient prevention programs, interactive, that will aim to target within the same protocol both anxiety and depressive symptoms.

**Trial registration:**

ClinicalTrials.gov: NCT02756507. Registered on 25 April 2016.

## Background

Anxiety and depressive disorders are highly prevalent in adolescents [1]. These disorders, also known as internalizing problems, pose important costs for the adolescent, in terms of affected social relationships, academic achievement, increased suicide risk [2]. The burden of these disorders is high for families and the society [3, 4]. Furthermore, given their chronicity (e.g., anxious disorders) and recurrence (e.g., mood disorders), internalizing problems are persistent [5, 6], being often important precursors of these conditions in early adulthood [7]. Internalizing problems in children and adolescents are related to impairments in functionality in the working field in early adulthood [8]. Moreover, along with the negative consequences and the burden of disease, another important aspect that should be considered is that internalizing problems are on the rise. Results of a systematic review showed that as compared with the twentieth century, over the twenty-first century there was an increase in internalizing problems in the adolescent population, especially for girls [9].

Preventing internalizing problems in adolescents could be an important aspect to target, as there is evidence that often anxiety and depressive disorders remain undetected, or even when they are diagnosed, a small percentage of adolescents receive adequate treatment [10, 11]. Several barriers to access mental health treatments refer to lack of information regarding treatments, stigma, or costs [12]. Another important barrier to receiving mental health treatment is related to adolescents’ health-seeking behaviors, namely they fail to recognize their emotional problems, and, consequently, they will not receive adequate treatment [13]. Schools are environments in which adolescents spent a high amount of time. Delivering prevention programs in a school format is cost-effective as shown by a review of Australian school delivered prevention programs for depression [14]. According to a recent meta-analysis, prevention programs delivered in a school context are promising, with small, however significant effects both at short- and long-term follow-up [15].

A main limitation of the existent universal prevention programs is the fact that there are no cross-over effects, specifically only those outcomes that are targeted (e.g., anxiety symptoms in universal prevention programs for anxiety) improve, with no significant changes in the non-targeted condition [16]. These findings call for more research into universal prevention programs that are based on transdiagnostic approaches, targeting both anxiety and depression within the same protocol. Research on transdiagnostic prevention programs delivered in school settings is scarce, with only a few studies being conducted [17–20] that show mixed results regarding the efficacy of transdiagnostic universal prevention programs on anxiety and depression outcomes at posttest, short- and long-term follow-up. However, given the high heterogeneity between these studies (e.g., treatment protocol, design, number of sessions) more research needs to be conducted in order to establish the efficacy of transdiagnostic universal prevention programs, as well as on the investigation of the mechanisms of change involved.

Rational emotive behavior therapy (REBT) [21, 22], a form of cognitive behavioral therapy (CBT), which emphasizes the role of irrational beliefs in generating dysfunctional emotions and maladaptive behaviors, has been previously tested as a prevention program for depressive adolescents [23], or as a brief intervention for adolescents with subclinical internalizing problems [24]. REBT is particularly suitable for a transdiagnostic universal prevention program, given the fact that according to its theory, irrational beliefs (e.g., demandingness, catastrophizing/awfulizing, low frustration tolerance and global evaluation of human worth) are transdiagnostic factors involved in emotional problems [25]. Furthermore, evidence coming from a meta-analysis shows that irrational beliefs are significantly associated with distress [26]. Furthermore, the suitability of REBT for transdiagnostic prevention and interventions programs is also indicated by those studies that show that several specific types of irrational beliefs are involved in multiple disorders (e.g., catastrophizing [27] or frustration intolerance [28]). REBT can be easily adapted for different modalities of delivering interventions, such as technologically enhanced interventions. No study, however, investigated the efficacy of an REBT prevention program delivered via technology enhancements.

Given the existent barriers in the access to mental health services, communication technologies (e.g., videos, text messages, Internet, smartphone apps) can overcome such barriers, improving the availability of mental health services in remote areas and also, reduce the costs [29]. Delivering universal school prevention programs with technological enhancements for adolescents could increase their engagement, improve their adherence to the program, and consequently, influencing the outcomes. For instance, a depression prevention program delivered in an Emergency unit, consisting of PowerPoint presentations supplemented with automated text messages, was found to be acceptable and feasible in a sample of adolescents [30]. Video-based treatments are effective for several conditions and populations, such as insomnia in cancer patients [31], anxiety symptoms in veterans [32], sleep problems in children [33], or aimed to reduce the stigma associated with mental illness in youths [34]. However, as far as we know, there are no studies investigating the efficacy of video-based prevention or intervention programs for adolescents with internalizing problems. Video-based prevention programs could be important to investigate, given the fact that videos are more appreciated by participants [35]; another benefit of video-based programs is the fact that they are cost-efficient [36].

### Study rationale

Given recent developments in communication technologies, mental health prevention programs for adolescents could overcome existent barriers in terms of access to evidence-based programs. Universal and indicated prevention programs facilitated through technology (e.g., delivered via smartphones, computers, Internet platforms) are promising in reducing anxiety, depression, and stress in students from higher education [37], with indicated prevention programs delivered with support being associated with better outcomes. Given the fact that most of the universal prevention programs delivered via technology were self-administrated, much research needs to be conducted in order to investigate the efficacy of such programs blended with face-to-face support from a mental health specialist. Moreover, the high comorbidity between anxiety and depressive disorders calls for the development and investigation of more efficient programs, which can target multiple problems within the same protocol. There is evidence that transdiagnostic interventions facilitated via technology are associated with moderate to large effect sizes in adult populations in what regards anxiety, depression, and quality of life outcomes [38]. Nonetheless, when considering young populations, research is scarce, with mixed results, few randomized controlled trials conducted and many confounding variables existing regarding the efficacy of transdiagnostic universal prevention programs facilitated via technology for anxiety and depression in adolescents. Schools are ecological environments that can be used in order to reach to a high number of adolescents, however much research needs to be conducted in order to investigate the efficacy of school-delivered universal prevention programs. There is a need for conducting more randomized controlled trials with larger samples of adolescents that could inform research not only about the effect that such a prevention program might have on adolescent related outcomes (e.g., reductions in anxiety, depression symptoms), but also, on the mechanisms of change, namely the active ingredients through which the intervention can influence those outcomes. Video-based programs have been so far tested as self-administrated interventions in both adult [31, 32] and young populations [33, 34], for health and emotional problems. Moreover, they hold great promises in terms of access to evidence-based programs, interactive content that can increase participants’ engagement and adherence to the program, limited input from the person that delivers the intervention.

### Aim

The present study aims to investigate the efficacy of a video-based transdiagnostic REBT universal prevention program for internalizing problems in Romanian adolescents, implemented in a school setting. Our second aim is to investigate subsequent mechanisms of change, namely, we want to investigate whether maladaptive cognitions are significant mediators of the prevention program’s efficacy.

## Methods/Design

The study design is reported according to the CONSORT 2010 (Consolidated Standards of Reporting Trials) Statement [39] and the SPIRIT 2013 (Standard Protocol Items: Recommendations for Interventional Trials) Statement [40].

### Design

A two-arm cluster randomized controlled trial (RCT) will be conducted. Participants’ school classes will be randomized by a computer software (www.randomizer.org) in one of the two treatment conditions: (1) video-based transdiagnostic REBT universal prevention program or (2) waitlist control. Assessments will be conducted at four time points: baseline (T_1_), post-intervention (T_2_), 3 months follow-up (T_3_) and 12 months follow-up (T_4_). Figure 1 illustrates the flowchart of the study.

**Fig. 1 Fig1:**
[figure not shown]
CONSORT diagram for the study

### Participants

#### Recruitment

Adolescents will be recruited from several public schools, namely from middle schools and high schools from Central, East and Nord West cities from Romania. School principals will be invited to participate and invitation letters containing information about the study will be offered to parents and adolescents.

### Eligibility criteria

#### Inclusion criteria

In order to be eligible for the present study, several inclusion criteria have been established:Preadolescents and adolescents will have ages between 12 and 17 years old;Are attending middle school or high-school;Adolescents have sufficient understanding of the Romanian language in order to complete assessments at all time points and to participate in the prevention program;Their parents have sufficient understanding of the Romanian language in order to sign the informed consent;Parents will sign the informed consent and adolescents will provide informed assent.

### Exclusion criteria

Age below 12 or above 17 years;No signed informed consent from parents;Adolescents will score high on suicidal ideation according to (1 item on the Depression subscale from Beck Youth Inventories [41]);Not Romanian-speaking in order to understand the content of the prevention program and to complete the assessments.

### Randomization and blinding

Randomization will be applied within classes, using a random numbers generator (www.randomizer.org), with an equal number of experimental and control groups within one school. Children will be assigned to either video-based transdiagnostic REBT universal prevention or to waitlist control condition. Allocation concealment will be done by an independent researcher, using opaque, sealed envelops that will be opened sequentially. Blinding of participants, researchers and assessors will be maintained.

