### Sample size calculation

A priori power analyses using G*Power version 3.1.5 [42] indicated that a total sample size of 260 would be sufficient to detect a small to medium effect size (*d =* .35) according to the results or previous research, for a two-tails between-group comparison at posttest, with an alpha of .05 and a power of 80%. As we expected to have a 30% dropout rate, we will recruit 169 participants in each group.

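### Classes are randomised according to the title and Design, but the randomisation wording conflicts with this, and neither the sample size nor the stated model allows for class

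*Protocol article*

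**What the plan says.** The unit of randomisation is described in several places in the protocol article.

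- Title: "study protocol of a cluster randomized controlled trial".
- Design: "A two-arm cluster randomized controlled trial (RCT) will be conducted", and participants' "school classes will be randomized by a computer software".
- Abstract, Methods: "A two-arm parallel randomized controlled trial will be conducted", with no mention of clusters.
- Randomization and blinding: "Randomization will be applied within classes, using a random numbers generator", continuing "with an equal number of experimental and control groups within one school". The next sentence adds: "Children will be assigned to either video-based transdiagnostic REBT universal prevention or to waitlist control condition".

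Sample size calculation states that "a total sample size of 260 would be sufficient to detect a small to medium effect size" (d = .35), for a two-tailed between-group comparison at posttest with alpha .05 and 80% power. It then sets recruitment at 169 per group to cover 30% dropout. It mentions no ICC, class size or number of classes.

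Statistical methods specifies mixed effects models with a random intercept, a random slope for time and a fixed effect of group. It names no term for class or school.

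**The concern.** Randomising inside a class sends classmates to different arms; randomising classes keeps them together. The section that sets the allocation rule uses words for the first, while the title and Design declare the second. Nothing in the article reconciles them.

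The unit of randomisation determines both the precision of the comparison and the valid analysis. Pupils in one class tend to resemble each other, and here they would also receive the programme together. If classes are allocated, 260 pupils carry less information than 260 independent pupils. The power is then below the stated figure, and an analysis that treats pupils as independent has standard errors that are too small. Correcting the wording of the randomisation section alone would leave that problem in place, because it comes from the sample size and the model.

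**Working it through.** **Inputs from the protocol article.** d = .35, two-sided alpha .05, power 80%, 260 evaluable (130 per arm), 30% dropout, 169 recruited per arm (338). The article gives no class size (m) and no ICC.

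**Step 1: reproduce 260.** A two-sample t-test of independent individuals at d = .35 needs 129.11 per arm, rounded up to 130, so 260 in total. Power at 130 per arm is 80.3%. The stated figure is matched exactly with a design effect of 1.

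**Step 2: reproduce 338.** 130 × 1.3 = 169 per arm, 338 in total. Losing 30% of 338 leaves 338 × 0.7 = 236.6, about 237, not 260. Retaining 260 would take 260 / 0.7 = 371.4, that is 372. With 237 independent pupils the power is 76.4%.

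**Step 3: assumptions for clustering.** I take ICC .02 to .05. For class size I take 25 analysed pupils as the upper value. The lower value is 25 enrolled less 30% dropout: 25 × 0.7 = 17.5. All of these are assumptions.

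**Step 4: formulas.**
- Design effect: DE = 1 + (m − 1) × ICC.
- Effective N = N / DE, with power from the two-sample t-test at that N.
- Type I error of a nominal 5% comparison that ignores class: 2 × (1 − Φ(1.96 / √DE)).

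For example, with m = 25 and ICC = .05: DE = 1 + 24 × .05 = 2.20; effective N = 260 / 2.20 = 118; 1.96 / √2.20 = 1.32, so type I error = 18.6%.

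| m | ICC | DE | Effective N of 260 | Power, 260 analysed | Power, 237 analysed | Type I error, class ignored |
|---|---|---|---|---|---|---|
| 17.5 | .02 | 1.33 | 195 | 68% | 64% | 8.9% |
| 17.5 | .05 | 1.83 | 142 | 55% | 51% | 14.7% |
| 25 | .02 | 1.48 | 176 | 64% | 59% | 10.7% |
| 25 | .05 | 2.20 | 118 | 47% | 44% | 18.6% |

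**Step 5: number of classes.** 260 pupils form about 260 / 25 = 10.4 to 260 / 17.5 = 14.9 classes over both arms. A valid class-level test therefore has few degrees of freedom. The calculation above makes no deduction for that, so these power figures lean towards the favourable side.

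**The case against.** The strongest reply is that the conflict rests on one preposition. The title and Design both say cluster trial, Design names the class as the unit, the programme is delivered in groups in pupils' school classes, and the balancing clause in the disputed sentence refers to groups within a school. The phrase is probably loose English for allocating by class within each school. That stands. The sentence saying that children are assigned also adds nothing to the conflict, since pupils in a randomised class are assigned too.

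A reader might go further and infer that programme and waitlist pupils will share classrooms, so that spillover dilutes the effect. That needs the literal reading, against which most of the text speaks, and the documents do not support it. A reader might also infer from the unadjusted sample size and model that individual allocation was intended. Omitting a design effect does not show which unit was meant.

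It can fairly be said that the power and type I error figures come from the sample size and model, not from the randomisation wording. That is correct, and they are attributed that way here. A condensed article may also leave model detail to an SAP that is not shown, so class may be handled there. This softens the point about the model. It does not help the power statement, which the article gives as complete and which matches only an unclustered calculation.

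Finally, carrying the last observation forward could bring more than 237 pupils into the analysis. The sample size section itself treats dropouts as lost, and the 237 follows that logic.

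**Conclusion.** The point holds as an inconsistency of wording with a consequential error behind it. Class allocation within school is the likely intent, and the stated 80% power is not a property of that design. Under the assumed 17.5 to 25 analysed pupils per class and ICC of .02 to .05, the design effect is about 1.33 to 2.20. Power with 260 analysed is then about 68% to 47%, and an analysis that ignores class has a type I error of about 9% to 19%. With the roughly 237 pupils left after the article's own dropout rate, power is about 64% to 44%.

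A reader might infer that the 80% would at least be right if pupils were allocated individually. The documents do not support that either: recruiting 338 with 30% loss gives about 76% before any clustering, and group delivery could produce some clustering in the programme arm even then.

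The direction of the error is certain for any positive ICC. Its size depends on a class size and an ICC that the article does not give. The type I error figures apply to a posttest comparison with no adjustment for class; adjusting for baseline could lower the relevant ICC.

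**What to change.** 1. **Randomization and blinding.** Replace the phrase about allocation within classes with: The school class is the unit of randomisation; within each school an equal number of classes is allocated to each arm, and pupils follow the allocation of their class. Give the abstract the same cluster design label.
2. **Statistical methods.** Add a random effect for class, and school as a factor because allocation is balanced within school.
3. **Sample size calculation.** In place of 80%, state the power for class randomisation at a stated ICC, class size and expected analysed number, with that number consistent with 338 recruited and 30% dropout.

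The cost is wording in the abstract and three sections, two model terms, a less favourable power figure and wider confidence intervals. No extra pupils are required, because the change reports the lower power openly and does not attempt to restore 80%. Restoring it would take more pupils: at DE 1.33 to 2.20, 260 becomes about 346 to 572 analysed.

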There are several limitations that we should consider. First, as we rely only on self-reported data, potential bias can result in the case of adolescents. Another important limitation could be the lack of a placebo condition. However, as this will be the first trial comparing the efficacy of a transdiagnostic video-delivered REBT prevention program, we aim to compare it with a waitlist condition and intend to extend this study and compare it with an active placebo or a traditional face-to-face program. Another limitation is related to the possible dropout at 12-month follow-up assessment, as it is possible that several adolescents entering high school will change their schools or live in a different city.

In conclusion, this is the first study that aims to investigate the efficacy of a video-based transdiagnostic REBT universal prevention program in reducing internalizing problems in adolescents. Also, it is the first study that integrated REBT with technology in the format of a video-based program aimed to reduce anxiety and depression outcomes in youths. Video-based interventions take into consideration young peoples’ predilection to use technology.

Moreover, as indicated in a recent review study analyzing school mental health programs delivered for more than 27 million of children [55], most of the research on the efficacy of prevention programs for children delivered in school contexts was conducted in high-income countries. We, therefore, need to conduct such a study in a Romanian population of adolescents, given the limited existent research on the efficacy of such programs in emerging countries.

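### Classes are balanced between arms only within school, so with few classes age and the classes about to enter high school can fall unequally on the arms by chance, and the stated model does not adjust for it

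*Protocol article*

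**What the plan says.** The Design section makes the class the unit of allocation: "school classes will be randomized by a computer software". Randomization and blinding words it differently, "Randomization will be applied within classes, using a random numbers generator", and then gives the only restriction on the draw: "with an equal number of experimental and control groups within one school". Neither section mentions grade or age.

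The population is wide in age. The inclusion criteria read "Preadolescents and adolescents will have ages between 12 and 17 years old", and Recruitment draws pupils "namely from middle schools and high schools from Central, East and Nord West cities from Romania".

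The Discussion lists as a limitation the chance of dropout at 12 months, and gives the reason: "it is possible that several adolescents entering high school will change their schools or live in a different city". It states no rate. T4 is one of the listed time points for both primary outcomes (Table 2).

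Statistical methods compares age between the arms at baseline by t-test. The efficacy model is described by a random intercept and slope for time and a fixed effect for group, with last observation carried forward (LOCF) at T2 to T4. No age, grade or school term is stated. Trial status says that recruitment continues.

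**The concern.** Classes in one school can differ by grade, and grade fixes age. If a school contributes a handful of classes and the draw only equalises their number, the older classes can land mostly in one arm. Age may be related to anxiety and depressive symptoms in this range (an assumption; the article gives no figure), so such a draw makes the arms less comparable and the contrast less precise.

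Grade also decides which pupils are about to move to high school, the only dropout mechanism that the article names. If the classes about to move are unevenly split, the arms can lose different numbers of pupils, from different age groups, by T4. With LOCF, earlier values would then stand in for T4 values more often in one arm, which can distort the T4 contrast. Nothing stated later in the plan takes this up: the baseline t-test on age leads to no adjustment.

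**Working it through.** **Inputs.** From the article: class as unit (Design), equal numbers of groups per arm within school (Randomization and blinding), ages 12 to 17 (Inclusion criteria), 338 recruits (Table 2). Not given: the number of schools and classes, the grade mix, and the T4 loss among pupils changing school. These are assumed below.

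**The plan's own figure.** The article states none for grade balance. Its total of 260 before dropout does reproduce (two-sample t-test, d = 0.35, two-sided 0.05, 80% power: 129.1, so 130 per arm), but grade plays no part in it. The 338 recruits serve here only to count classes: 338/30 = 11.3 and 338/15 = 22.5, so about 11 to 23 classes at 15 to 30 pupils each. I use layouts of 12 to 16.

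**Step 1: mean age, 4 schools x 4 classes of equal size.** The arm difference D is one eighth of the sum, over schools, of (ages in arm A minus ages in arm B).

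- School balance only: within a school the bracket has variance 4S², where S² is the variance of the four class ages (divisor 3). So Var(D) = 4 x 4S²/64 = S²/4.
- Classes paired by nearest grade, with age gaps g1 and g2 within pairs: the bracket is ±g1 ±g2, so Var(D) = 4(g1² + g2²)/64 = (g1² + g2²)/16.

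| Grade mix in a school | S² | SD, school only | g1² + g2² | SD, paired |
|---|---|---|---|---|
| Random from three grades (averages) | 0.667 | 0.41 y | 1.185 | 0.27 y |
| Random from four grades (averages) | 1.25 | 0.56 y | 2.125 | 0.36 y |
| One class in each of four grades | 1.667 | 0.65 y | 2 | 0.35 y |

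Pairing removes about a third to almost a half of the SD. In the three-grade mix, the chance of a difference of at least half a year under school balance alone is about 28% to 29%.

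**Step 2: mean age, 7 schools x 2 classes of different grades (from three).** The gap is 1 year with probability 2/3 and 2 years with probability 1/3, so the mean squared gap is 2/3 + 4/3 = 2. Var(D) = 7 x 2/49 = 0.286, SD 0.53 years, and the chance of at least half a year is about 36%. Pairing changes nothing here, because the two classes are already split one to each arm. If both classes share a grade, the imbalance is nil.

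**Step 3: split of the classes about to enter high school.** The number falling in one arm is hypergeometric within a school, summed over schools.

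| Schools x classes | Transition classes per school | Chance that arms differ by 2 or more |
|---|---|---|
| 3 x 4 | 1 | 25% |
| 3 x 4 | 2 | 59% |
| 4 x 4 | 1 | 62.5% |
| 4 x 4 | 2 | 65% |
| 6 x 2 | 1 | 69% |
| 7 x 2 | 1 | 45% |
| 2 x 6 | 2 | 56% |
| 2 x 8 | 2 | 58% |

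For 4 x 4 with one such class per school this is Binomial(4, 0.5): 2:2 has probability 6/16, so an unequal split has 10/16 = 62.5% (3:1 in 8/16, 4:0 in 2/16).

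**Step 4: what that could mean at T4.** Take 8 classes per arm and assume that half of the pupils in transition classes are lost. A 3:1 split gives (3/8) x 0.5 = 19% against (1/8) x 0.5 = 6%. A 4:0 split gives 25% against 0%. The one half is an assumption, and the loss scales with it in proportion.

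**The case against.** Several counter-arguments have force.

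- **Chance imbalance under a valid draw is not bias.** This stands. A reader might infer that the allocation rule biases the trial; it does not. The loss is in precision and comparability.
- **The article does not predict whole-class loss.** A reader might infer that final-grade classes are bound to be lost. The text says only "Another limitation is related to the possible dropout at 12-month follow-up assessment", for several adolescents and as a possibility, and it concerns pupils entering high school, not the last year of high school. Calculations that remove every pupil of such classes go beyond it.
- **Age adds no further variance on top of clustering.** A reader might add an age component to the between-class variance of the contrast. Age differences between classes are already part of that variance, so this would count them twice. No variance inflation is claimed.
- **Pairing within school does not always help.** This stands for two classes of different grades (Step 2) and for a single transition class in a school, which still goes to either arm with probability one half.
- **A baseline is measured.** So far as the comparison is of change from T1, a stable age difference in level matters less, and only age-related change would disturb it. This stands in part; it does not touch unequal T4 loss.
- **Middle and high schools may be separate.** Balance within school then already controls the widest age contrast, and the spread within a school is narrower than 12 to 17. This is why the table uses three or four grades.
- **A condensed article may omit a grade factor, and its wording of the unit is inconsistent.** Both are fair. The article does report the school restriction, however, and a grade restriction would naturally stand beside it. If pupils were randomised inside classes the point would vanish, but the title, the Design section and the reference to groups within a school all indicate the class.

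**Conclusion.** The point holds in a limited form. The stated draw controls school but not grade, the stated model controls neither age nor grade, and the article itself links possible T4 loss to a particular grade. With few classes an uneven split is an ordinary outcome: 25% to 69% for a gap of two or more transition classes over the layouts tried, and an SD of 0.41 to 0.65 years for the arm difference in mean age with four schools of four classes.

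These sizes rest on assumed numbers of schools and classes, grade mixes and loss rates. They would shrink if classes in a school share a grade or if few pupils change school. The effect of age on the outcomes is not given in the article and is not quantified here. This is a design weakness with a cheap remedy, not an error in a stated figure.

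**What to change.** 1. In Randomization and blinding, state that the class is the unit, in agreement with the Design section.
2. For schools not yet drawn that contribute four or more classes: pair classes of the same grade, or of the nearest grade where there is no match; draw one of each pair to each arm; and draw all pairs of a school in one step, so that later assignments cannot be guessed.
3. Where schools have a single class about to enter high school, balance those classes across schools, for example by drawing two such schools together with their transition classes going to opposite arms. With four such schools this gives 2:2; an odd number leaves a difference of one.
4. For all schools, including those already drawn, add age (already collected) or grade as a fixed covariate in the primary model. If the contrast is on change over time, include its interaction with time, since a main effect alone adjusts only level. In schools with two classes of different grades this is the remedy for age imbalance, because pairing gains nothing there.
5. Report T4 retention by grade and arm.

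The cost is a few sentences in the randomisation and analysis text, with no extra pupils, visits or measures. The limits are small: a nearest-grade rule has to be written, balancing across schools means drawing some schools together, and items 2 and 3 reach only schools not yet drawn.
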